#### Concomitant care

All patients in the study will receive the routine standard of care. This will include a check of blood and vital parameters, a neurologic investigation and CT scan at admission. An acute onset of neurologic deterioration or a decline of alertness will need an urgent operative treatment. For neurosurgical procedures normal coagulation parameters are essential. In warfarin medication, the international normalized ratio (INR) has to be normal prior to surgery. Coagulation factors or other blood products will be administered as required. ASS is to be stopped five days and GpIIb/IIIa-receptor antagonists seven days before surgery, and NOAC a duration longer than double of their pharmacological half-life. Only those patients are eligible who are able either to pause their anticoagulant or antiplatelet medication, or to tolerate a conversion to LMWH (low molecular weight heparin) for two weeks postoperatively.

In consideration of different techniques available for the evacuation of a chronic subdural hematoma, the following procedure has been agreed: one burr hole over the site of the hematoma, no irrigation and a closed drainage system. The drain will be continued up to 48 hours. Criteria for discontinuing before 48 hours are air in the system, an incorrigible flow arrest or delivery of pure CSF.

Pain will be treated according to the WHO guidelines
[29].

LWMH are used for deep venous thrombosis prophylaxis. The application has to start within 24 hours postoperatively, or if the patient is mobile, less than 3 hours a day. Daily neurologic investigations and control of vital parameters and wound healing will be added to standard care, as will concerted medication and drawing of blood samples, CT scans and physical therapy as necessary.

There will be a focus on hyponatremia and pathologic INR values. Patients who received oral anticoagulation preoperatively will need to be controlled daily and will have to have their parameters kept within the normal range throughout the hospital stay. The same procedure will be applied in hyponatremia. At study day-3 blood glucose levels are evaluated. At a level higher than 300 mg/dl the patient will be excluded from the trial. In order to detect a raised intraocular pressure a measurement will be performed during the treatment period.

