#### Secondary Outcome Measures

Secondary outcomes include clinical evaluation by the Markwalder score and radiologic characteristics of the CT/MR images over time. On axial CT scans the thickness of the hematoma and midline shift is measured in millimeters at the thickest area and the volume is calculated in cubic centimeters. Midline shift is measured at the level of the intraventricular foramen. Hematomas are classified as homogenous, laminar, separated or trabecular. Their location is classified as being over the convexity, at the cranial base or the interhemispheric space. There is also a focus on brain atrophy that is classified as none, mild, definite, or severe. Residual air is measured in cubic centimeters. The influence of a patient’s long-term medication is evaluated together with coexisting diseases as predictors for recurrence.

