### Data analysis

The primary endpoint is the rate of reoperation between 48 hours and 12 weeks after the initial evacuation of a chronic subdural hematoma. Mandatory reoperation during the first 48 hours is related to surgical complications. In such rare cases the patient will be excluded.

Evaluation of the Markwalder score will be done by computing crosstabulation tables and applying Pearson’s chi-square test. Data will be checked carefully for outliers and for normality based on the Kolmogrov-Smirnov test and Liliefors test. To evaluate the impact of dexamethasone on the thickness of the hematoma and other continuously distributed, metrically scaled variables, mixed models with treatment group as the independent factor and time as the repeated factor will be applied (if all assumptions for the model are met). Linearity will be assessed by Box Tidwell and log transformation. Corresponding planned contrasts together with 95% confidence intervals will be computed. If these variables do not fulfill the assumptions for parametric testing, nonparametric methods such as the bootstrap *t*-test, Kruskal-Wallis analysis of variance (ANOVA) with median tests and Friedman ANOVA with Wilcoxon matched-pairs test will be applied: 95% confidence intervals based on Pearson-Clopper values will be computed to estimate the reoperation rate in both groups. An unconditional test (Barnard’s test for superiority) for the ratio of these two proportions will be used. A *P*-value less than 5% will be considered statistically significant. All analyses will be done by one of the authors (WH) using STATISTICA 10 (Hill, T and Lewicki, P (2011). *STATISTICS: Methods and Applications*. StatSoft, Tulsa, OK, USA), StatXact 6.0 (Cytel Software Corporation (2003) Cytel Software Corporation, Cambridge MA, USA), NCSS 8 and PASS 11 Hintze, J (2012), NCSS 8, NCSS, LLC, Kaysville, UT, USA. (http://www.ncss.com).

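### Whether the secondary continuous imaging outcomes keep their mixed model depends on assumption checks that use sensitive normality tests, and no listed fallback gives a treatment effect over time

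*Protocol article*

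**What the plan says.** The Secondary Outcome Measures section of the protocol article defines the imaging variables: "On axial CT scans the thickness of the hematoma and midline shift is measured in millimeters at the thickest area". Volume and residual air are in cubic centimeters. The recording resolution is not given. Concomitant care provides for "a neurologic investigation and CT scan at admission". Table 2 adds a scan within 48 hours of surgery and scans at weeks 4 and 12, plus one at week 24 after reoperation only.

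The Data analysis section then sets out a sequence:

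- **Check:** "Data will be checked carefully for outliers and for normality based on the Kolmogrov-Smirnov test and Liliefors test".
- **Model:** "treatment group as the independent factor and time as the repeated factor will be applied (if all assumptions for the model are met").
- **Output of the model:** "Corresponding planned contrasts together with 95% confidence intervals will be computed". The contrasts are not specified.
- **Switch:** "If these variables do not fulfill the assumptions for parametric testing, nonparametric methods such as the bootstrap" t-test are used instead.
- **Rest of the list:** "Kruskal-Wallis analysis of variance (ANOVA) with median tests and Friedman ANOVA with Wilcoxon matched-pairs test will be applied".

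The section does not say whether normality is tested on raw values or model residuals, per arm or pooled, or which of the two normality tests governs if they disagree.

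**The concern.** This is a stated switching rule, so it is not simply detail left to a statistical analysis plan. Three features make it a poor one.

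1. Normality is the only distributional assumption with named tests. With several hundred patients, a significant normality test says little about whether a mixed-model comparison of arm means is trustworthy. Rounding, mild skew or a cluster of zeros can be enough to reject.
2. The wording refers to data and to variables, which points towards raw values. A mixed model makes its distributional assumptions about residuals and random effects.
3. The fallback list is open, so the choice of test can be made after the data have been seen, and no listed test handles treatment and time together.

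At stake is the radiologic secondary objective. If the switch is made, the treatment contrast over time and its confidence interval go, and a set of separate tests takes their place. Friedman also needs a complete set of visits per patient. The Sample size section raises 370 to 410 per arm for drop-out, that is 40/410 = 9.8%, so incomplete series are expected.

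**Working it through.** **Sample size used.** The Sample size section gives 370 evaluable patients per arm and 83% power for 10% against 5%, one-sided 5%. Against equal rates, with mean rate 0.075:

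z = [0.05 × √370 − 1.645 × √(2 × 0.075 × 0.925)] / √(0.10 × 0.90 + 0.05 × 0.95) = (0.9618 − 0.6127) / 0.3708 = 0.941, so power is 82.7%.

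Exact enumeration of the score test gives 82.6% to 83.3%. The plan's figure reproduces, so n = 370 (one arm) and n = 740 (pooled) are the right sizes here. The protocol states no figure for the imaging outcomes.

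**Why rounding matters.** Simulated 5% critical values of the Lilliefors distance are 0.0467 (n = 370) and 0.0335 (n = 740). Uncorrected Kolmogorov-Smirnov uses 0.0701 and 0.0497. Rounding to a step h makes the empirical distribution jump by about 0.399 × h/SD at the center. Even perfectly normal data are then at a distance of about half of that, before sampling noise:

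- h = 1 mm, SD 5: 0.399/(2 × 5) = 0.040, above the critical value at n = 740 and close to it at n = 370.
- h = 1 mm, SD 9: 0.399/(2 × 9) = 0.022.
- h = 0.1 mm, SD 5: 0.399 × 0.1/(2 × 5) = 0.004, negligible.

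The harm to a mixed model is trivial. Rounding to whole mm adds a variance of about 1/12 = 0.083 mm², which at SD 5 is 0.083/25 = 0.3%.

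**Simulated Lilliefors rejection at the 5% level.** SDs, shapes and resolution are assumptions. Most rows use 1000 data sets per setting, with a standard error of at most √(0.25/1000) = 1.6 points. A range in a cell shows repeated runs or, in the 0.1 mm row, several SDs.

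| Assumed values | n = 370 | n = 740 |
|---|---|---|
| Normal, whole mm, SD 5 | 98-99% | 100% |
| Normal, whole mm, SD 7 | 72% | 99% |
| Normal, whole mm, SD 9 | 48-49% | 85-87% |
| Skewness 0.5, 0.1 mm | 81% | 99% |
| Skewness 0.63 | 82-88% | 99-100% |
| 5% zeros, remainder normal, 0.1 mm | 46% | 86% |
| 10% zeros, remainder normal, 0.1 mm | 99-100% | 100% |
| Normal, 0.1 mm, SD 3 to 9 | 6-8% | 5-11% |
| Baseline-adjusted residuals of whole-mm normal data (SD 6, correlation 0.4) | 7.6% | 7.6% |

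Uncorrected Kolmogorov-Smirnov rejects less often: 3%/18% for whole-mm normal data with SD 7, against 72%/99% for Lilliefors. The two named tests can therefore disagree on the same data.

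**What each fallback estimates.**

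| Method | Compares arms? | Treatment effect over time? |
|---|---|---|
| Bootstrap t-test | Yes, one time point or summary | No |
| Kruskal-Wallis with median test | Yes, one time point or summary | No |
| Friedman | No, time points within patients | No |
| Wilcoxon matched-pairs | No, time points within patients | No |

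**Value of the baseline scan.** Adjusting for it multiplies the variance of the arm comparison by 1 − ρ²: 1 − 0.09 = 0.91 at ρ = 0.3, 0.75 at ρ = 0.5 and 0.64 at ρ = 0.6. The documents give no ρ.

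**The case against.** Four arguments on the other side deserve weight.

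- **A reader might infer that the fallback abandons the comparison of arms for within-arm tests.** The text does not support this. The bootstrap t-test and Kruskal-Wallis can both compare dexamethasone with placebo, and the list may simply mirror the model's two factors. Nothing says that within-patient results will be read as treatment effects. What is lost is the joint treatment-by-time estimate.
- **A reader might infer that the switch will nearly always be triggered.** That is not established. Millimeters are a unit, not a resolution; the rounding, skew and zeros above are assumed. Near-normal values at 0.1 mm, or near-normal residuals, are rejected at close to the nominal rate. The rounding argument does not carry over to variables in cubic centimeters. The switch is also worded in terms of parametric assumptions generally, with no p-value cut-off for a normality test.
- **A reader might count the missing baseline covariate as an error.** It is not one. The article is silent on covariates, which are commonly left to the full protocol or analysis plan, and the admission scan may enter as a level of the time factor.
- **The plan already mentions log transformation (for linearity) and a bootstrap method**, so part of the remedy is close to what is there.

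All four stand. They narrow the point but do not remove it: the method still depends on the outcome data, by a criterion that is not fixed, and leads to an open list without a treatment effect over time.

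**Conclusion.** The point holds as a cheap improvement to the analysis of the secondary continuous imaging outcomes. The switch away from the mixed model is driven by the data and supported by normality tests that, at 370 or 740 patients, can reject for harmless reasons. How likely this is depends on details that the article does not give: from about 7-8% for near-normal values at 0.1 mm to 99% or more for whole-mm values with SD 5 or for 10% zeros, if Lilliefors is run on raw values. Skew and zeros are plausible for measurements that cannot fall below zero after evacuation, but this is an assumption. If the switch is made, the arms can still be compared one time point at a time, but the treatment effect over time with its confidence interval is lost. The primary endpoint, with its own unconditional test and exact intervals, is not affected.

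**What to change.** Make the mixed model the analysis of each continuous imaging outcome whatever the normality tests show.

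- **Terms:** treatment, visit, treatment-by-visit, the screening CT value as covariate (or a model with baseline constrained equal across arms), and site, which is the stratification variable.
- **Report:** the dexamethasone-minus-placebo contrasts at weeks 4 and 12 with 95% confidence intervals.
- **Checks:** judge residuals graphically. Where they are skewed, use a log transformation or bootstrap confidence intervals for the same contrast.
- **Remove:** Friedman and Wilcoxon matched-pairs as treatment comparisons. They may stay as descriptions of change over time.

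The cost is wording in the analysis plan and a little more model checking; no data need be added. It should be settled before unblinding.

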#### Secondary objectives

The secondary objectives of the study are as follows: to measure the effect of dexamethasone on clinical outcome by the Markwalder score during a period of 12 weeks after surgery; the impact on radiologic signs of the hematoma, such as thickness, membranes and mass-demanding effect (midline-shift); to evaluate risk factors of the genesis and recurrence of cSDH in a prospective study design; risk of infectious complications, for example, pneumonia, urinary tract infection, ventriculitis, meningitis and encephalitis; dexamethasone-dependent severe psychiatric reactions; and death.

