### Sample size

Let p_verum_ be the reoperation rate in the verum group and p_placebo_ be the reoperation rate in the placebo group. The null hypothesis H_0_ is that the ratio of both rates p_placebo_ /p_verum_ is equal or smaller than 2, the corresponding alternative hypothesis H_1_ is that the ratio p_placebo_ /p_verum_ is larger than 2. In other words, the alternative hypothesis states that dexamethasone reduces the reoperation rate by 50% or more. For a reasonable medication the effect size is assumed to be this size because dexamethasone will be taken by the majority without benefit.

The assumed reoperation rate p_placebo_ is 10%. This is in accordance with the data from our department and the Chinese study sites. In order to detect a ratio p_placebo_ /p_verum_ of 2 or more with a power of 80%, the sample sizes are n1 = n2 = 370 in each arm. The type I error is 5% and the type II error for this scenario is 20%. The actual power of 83% is based on the exact power for the ratio of two binomial populations, one-sided and based on the score test (StatXact Cytel Software Corporation (2002) *StatXact 6.0 For Windows User Manual*, Cytel Software Corporation, Cambridge MA, USA). Due to possible drop-out of patients, we increased the sample sizes up to 410 in each group. Thus, 820 patients undergoing surgery for cSDH will be included.

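### The primary test is valid but uses neither study site nor the baseline data the trial already collects, so a small amount of precision is forgone

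*Protocol article*

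**What the plan says.** The endpoint is binary: "The primary endpoint is the rate of reoperation between 48 hours and 12 weeks after the initial evacuation of a chronic subdural hematoma". The Data analysis section fixes the comparison: Barnard's unconditional test "for the ratio of these two proportions will be used". Clopper-Pearson intervals are given for each arm. No covariate or site term enters, and no adjusted analysis of reoperation is described.

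The Randomization section stratifies by study site and by nothing else.

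Table 2 schedules a CT scan, the Markwalder score, medical history and concomitant medication at screening. Its footnotes have medication recorded from two weeks before study drug and require a repeat scan when the only baseline CT is a hardcopy film. Scans are read centrally and blinded. The Secondary Outcome Measures section defines thickness, volume and midline shift on CT, and adds: "Hematomas are classified as homogenous, laminar, separated or trabecular".

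The trial also looks for baseline predictors. One secondary objective is "to evaluate risk factors of the genesis and recurrence of cSDH in a prospective study design", and under Secondary Outcome Measures long-term "medication is evaluated together with coexisting diseases as predictors for recurrence". The Methodology section of the discussion expects to learn about risk factors, co-medication and radiologic findings.

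**The concern.** A two-sample test of proportions cannot use covariates. If any baseline factor predicts reoperation, adjusting for it sharpens the treatment comparison using data already on file. Site is normally the first candidate, because the randomisation is stratified on it.

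The number of primary events is small (about 55, see the working), so precision is worth having. The protocol also plans to analyse risk factors for recurrence. If the adjustment set is not fixed beforehand, an adjusted treatment effect could later be built from whichever factors turned out to matter.

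**Working it through.** **Inputs.** From the Sample size section: placebo rate 10%, a halving to 5%, 370 per arm before the drop-out allowance and 410 after it, one-sided score test, alpha 5%, stated power 83%. Assumed, because the documents give no figure: the prognostic strength of the baseline covariates. I write it as s, the SD of the logistic linear predictor, from 0 to 1.3 (AUC 0.50 to 0.80).

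**1. The plan's own figure.** Normal approximation, one-sided test of equal rates:

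- Null SE = √(2 × 0.075 × 0.925 / 370) = 0.01936
- Alternative SE = √((0.10 × 0.90 + 0.05 × 0.95) / 370) = 0.01928
- Power = Φ((0.05 − 1.645 × 0.01936) / 0.01928) = Φ(0.94) = 82.7%

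Exact binomial enumeration of the pooled score test gives 83.3% at the nominal cut-off and 82.6% at a Barnard-type exact cut-off. The stated 83% is reproduced, and it comes from an unadjusted test of a ratio of 1. With all 410 per arm analysed, the exact power is 86.6% and 86.0% at the same two cut-offs.

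**2. Expected events.** 370 × (0.10 + 0.05) = 55.5.

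**3. Power with adjustment.** 5,000 simulated trials per setting with four normal baseline covariates, intercepts solved so that the marginal rates stay at 10% and 5%. The adjusted test is a logistic model with treatment and the four covariates, standardised to a risk difference with an influence-function SE. Both tests use the one-sided cut-off 1.645.

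| s | AUC | Unadjusted, 370 per arm | Adjusted, 370 per arm | Gain (points) | Gain at 410 (points) |
|---|---|---|---|---|---|
| 0 | 0.50 | 83.9% | 84.0% | 0.1 | 0.1 |
| 0.5 | 0.64 | 84.0% | 84.7% | 0.7 | 0.7 |
| 0.8 | 0.71 | 82.4% | 84.0% | 1.6 | 1.1 |
| 1.0 | 0.75 | 83.3% | 86.2% | 2.9 | 1.9 |
| 1.3 | 0.80 | 83.2% | 87.2% | 4.0 | 3.9 |

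The Monte Carlo SE of one entry is √(0.83 × 0.17 / 5000) = 0.5 points, so the spread in the unadjusted column is noise. Type I error at 10% in both arms was 5.4% (s = 0) and 4.9% (s = 1.0) adjusted, against 5.3% and 4.8% unadjusted.

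A separate simulation with one covariate (9,000 trials per setting) gave 83.6% to 84.0%, 83.2% to 84.6% and 83.0% to 85.2% for odds ratios of 1.5, 2.0 and 2.5 per SD. These are s = ln 1.5 = 0.41, ln 2.0 = 0.69 and ln 2.5 = 0.92, so they agree with the table.

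**4. The same in patients.** The large-sample variance ratio of adjusted to unadjusted is 0.982, 0.953, 0.925 and 0.876 for s = 0.5, 0.8, 1.0 and 1.3. Multiplied by 370, the adjusted analysis would need about 363, 352, 342 and 324 per arm.

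**5. Chance imbalance.** A factor present in half the patients differs between arms with SD √(0.25 × 2 / 370) = 3.7 percentage points. For a continuous covariate, a 2-SE imbalance is 2 × √(2/370) = 0.147 SD. With an assumed odds ratio of 2 per SD, this is 0.147 × ln 2 = 0.10 on the log-odds scale and moves a true ratio of 2.0 to about 1.83 or 2.19, a log-ratio shift of ln(2.19/2.0) = 0.09. The SE of the log ratio with 37 and 18.5 events is √(1/37 − 1/370 + 1/18.5 − 1/370) = 0.275, so the shift is about 0.09/0.275, a third of a standard error.

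**The case against.** The strongest reply is that nothing here is wrong. Barnard's test is valid for a 1:1 randomised binary endpoint and matches the sample-size method. The trial is planned at 83% against a target of 80%, with more patients enrolled than that needs. All of this stands.

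A reader might infer that the trial loses material power. The documents do not support that: they give no prognostic strength, and a gain of 3 to 4 points needs AUC 0.75 to 0.80.

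A reader might also infer that chance imbalance biases the result. It does not. The test's type I error already allows for it, a 2-SE imbalance in a given covariate arises about once in 20 trials, and step 5 puts its effect at a third of a standard error even for a strong covariate.

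Nor do the documents name volume, architecture or Markwalder grade as predictors. Only long-term medication and coexisting diseases are so named; the CT features and clinical grade appear as outcomes over time. Their use as covariates rests on the general risk-factor objective and on the discussion's interest in radiologic findings.

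Finally, the simulated covariates were normal and correctly specified, and site was not simulated. The model proposed below will not match that exactly. The gain is also not free, since exactness is given up.

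These points limit the claim without removing it. In both simulations adjustment held type I error near 5% and lost no power, even with uninformative covariates. The protocol has chosen a test that excludes adjustment, so this is not a detail left open for an analysis plan.

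**Conclusion.** The point holds as a modest improvement to a valid analysis. The primary test leaves out site and all baseline data, and so forgoes a little precision. At 370 per arm the cost is about 0 to 2 points of power if the covariates are weak to moderate (AUC up to about 0.71), and up to about 4 points at AUC 0.80. These figures assume 10% versus 5%, a one-sided 5% test of a ratio of 1, and a prognostic strength that the documents do not supply.

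The Sample size section writes the null as a ratio of at most 2, with the alternative that "the alternative hypothesis states that dexamethasone reduces the reoperation rate by 50% or more". The 83% does not belong to that null: at a true ratio of 2, a test of it has power of about the 5% alpha. That is a separate and larger problem, and adjustment does not cure it.

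**What to change.** Pre-specify as the primary analysis a logistic model for reoperation with treatment, site (small sites pooled, or country) and two or three covariates measured before surgery, for example baseline haematoma volume, pre-operative antithrombotic use, and architecture collapsed to two classes. Keep the set small: treatment, a two-country term and three single-parameter covariates make 5 terms on about 55 events, or 11 events per term. All four architecture classes would add two terms and bring this down to about 8.

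Standardise the model to a marginal risk ratio and risk difference with confidence intervals, and test the null of a ratio of 1. Keep Barnard's test as the supporting unadjusted analysis. Do not use the day-2 CT as a covariate, because it can follow the start of study drug.

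The change costs analysis wording only; no new data are needed. The primary p-value is then no longer exact, and a simple rule for missing baseline CT reads must be written in advance.
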